### Data monitoring and safety committee

A data safety committee carries out an interim analysis after activation of cluster 3. The committee reviews prehospital times and especially prehospital on-scene time. A significant increase in onset-to-hospital time is acceptable only if onset-to-needle time (i.e. door-to-needle time) is reduced.

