## Background

Early identification of stroke symptoms and patient selection is an important factor for outcome and prognosis in acute stroke patients [1, 2]. Prehospital delay, time from onset to hospitalisation, may alone account for the largest proportion of total delay [3]. Less than 50% of stroke patients in Norway reach hospital within 4 h, which reduces the likelihood of successful acute treatment [4]. A unique feature of the Norwegian prehospital system is that all patients have to be conferred with an in-hospital doctor before hospitalisation. This means that all suspected stroke patients have to be conferred with a on-call doctor before arrival. Based on this prenotification the decision is made if the patient is to be assessed by the stroke team.

A combination of early prehospital identification of stroke, triage to the right level of care and improvement of in-hospital measures to reduce door-to-needle time may result in more patients receiving acute treatment [5]. Lower quality of communication between paramedics and stroke centre significantly increases prehospital on-scene time [6]. In a consensus statement from the European Academy of Neurology (EAN) and the European Stroke Organisation (ESO), training paramedics in recognising symptoms of all stroke types was strongly recommended [7].

National Institutes of Health Stroke Scale (NIHSS) is the most frequently used stroke scale to quantify stroke symptoms [8, 9]. It is composed of 11 items and higher scores indicate more severe strokes [8]. NIHSS has been introduced to the prehospital field and anaesthesiologists trained in prehospital critical care have shown to effectively assess NIHSS with good interrater agreement compared to an in-hospital stroke team physician [10].

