### Outcome measures

#### Primary outcome measure

The primary outcome measure is positive predictive value (PPV) for prehospital identification of patients with acute stroke. This will be calculated using study patients discharged with a stroke diagnosis (true positive) divided by all study patients seen by the stroke team (both true and false positive). Secondary outcomes are listed in Table 2.

**Table 2 Tab2:** Secondary outcome measures

Outcome measure	Cohort 1 Suspected stroke	Cohort 2 Final diagnosis of stroke
Prehospital on-scene time	X	X
Onset-to-hospital time	X	X
Onset-to-treatment time	X	X
Interrater agreement between paramedics and admitting stroke physician	X	X
Absolute change in NIHSS from prehospital to; admission, 2 h post admission, 24 h post admission and at discharge	X	X
Number of patients with suspected acute stroke admitted to the stroke unit	X	X
Number of patients with confirmed acute stroke diagnosis	X	
Door-to-(first) brain imaging time interval	X	
Number of patients receiving IVT	X	X
Door-to-needle time in patients receiving IVT	X	X
Number of patients with symptomatic post-thrombolysis haemorrhage	X	X
Number of patients receiving EVT		X
Door-to-groin-puncture time in patients receiving EVT		X
mTICI score		X
Door-to-needle time for blood pressure lowering in patients with ICH		X
NIHSS at discharge		X
NIHSS at 90-day follow-up		X
Modified Rankin Scale (mRS) at 90-day follow-up		X
Identified LVO, anterior and posterior		X
ASPECTs		X
Infarction volume (MRI/CTP)		X

*mTICI* modified thrombolysis in cerebral infarction [28], *ICH* intracranial haemorrhage, *ASPECTs* Alberta Stroke Program Early CT score [29]

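### The committee's only stated acceptance condition treats onset-to-needle and door-to-needle time as one interval, so it could be met while total delay to treatment is longer

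*Protocol article*

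**What the plan says.** The section on the data monitoring and safety committee sets one interim look: "A data safety committee carries out an interim analysis after activation of cluster 3". On its content it says: "The committee reviews prehospital times and especially prehospital on-scene time". It then gives its single decision condition: "A significant increase in onset-to-hospital time is acceptable only if onset-to-needle time (i.e. door-to-needle time) is reduced". It states no size of reduction and no population for either interval.

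Elsewhere the article separates the intervals that this sentence merges:

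- Table 2 (secondary outcomes) has one row for "Onset-to-hospital time", another for "Onset-to-treatment time" and a third for "Door-to-needle time in patients receiving IVT".
- The Background describes the time before arrival as a component in its own right: "Prehospital delay, time from onset to hospitalisation, may alone account for the largest proportion of total delay".
- The Background places door-to-needle time inside the hospital, referring to "improvement of in-hospital measures to reduce door-to-needle time".

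Nothing in the article says which of the two intervals the committee is to use.

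**The concern.** The condition is about a trade-off. If the ambulance phase becomes longer, something must improve in return. Onset-to-needle time contains the ambulance phase, so it shows whether the trade has paid off for treated patients. Door-to-needle time starts at the hospital door and contains none of the delay being traded. By joining the two with an i.e., the sentence leaves open whether the prehospital delay counts in the test at all.

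The trial replaces a short screening tool with an 11-item scale in the ambulance, and the committee is told to look at on-scene time in particular, so a longer prehospital phase is a foreseen risk. If the parenthesis governs, the one stated condition could be satisfied while treated patients reach treatment later than before.

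**Working it through.** The article gives no minutes for any of these intervals and no figure to reproduce. The check is therefore an identity, evaluated on assumed changes.

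**Inputs.** The condition comes from the section on the data monitoring and safety committee. The intervals come from Table 2 and the Background. All minutes below are assumptions.

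**Identity.** For one treated patient:

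onset-to-needle = onset-to-hospital + door-to-needle

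The two needle intervals are equal only if onset-to-hospital time is zero, yet the condition comes into play exactly when that time has increased.

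**Changes between groups.** Let H be the rise in mean onset-to-hospital time and D the fall in mean door-to-needle time, both in the same treated patients. The change in mean onset-to-needle time is H - D. This holds for means; medians need not add exactly.

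**The two readings, with H > 0:**

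- Read as door-to-needle time, the condition is met if D > 0.
- Read as onset-to-needle time, it is met if H - D < 0, that is, if D > H.

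The readings disagree when 0 < D ≤ H. Total delay is strictly longer when 0 < D < H and unchanged when D = H. The disagreement runs one way only: if D > H > 0, then D > 0 as well, so within the same patients the door-to-needle reading is never the stricter one.

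**Illustration (assumed minutes):**

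| Onset-to-hospital | Door-to-needle | Onset-to-needle | Met, read as door-to-needle | Met, read as onset-to-needle |
|---|---|---|---|---|
| +5 | -2 | +3 | yes | no |
| +15 | -5 | +10 | yes | no |
| +20 | -2 | +18 | yes | no |
| +10 | -10 | 0 | yes | no |
| +10 | -15 | -5 | yes | yes |

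**Populations.** Table 2 lists onset-to-hospital time for all suspected strokes as well as for confirmed strokes, whereas door-to-needle time exists only in patients given thrombolysis. A rise seen in all suspected strokes cannot simply be added to a fall seen in the treated subset. The identity and the table apply within treated patients, and the article does not say in which patients either half of the condition is judged.

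**The case against.** **The condition is necessary, not sufficient.** A reader might infer that any fall in door-to-needle time automatically excuses a longer prehospital phase. The wording does not say so. It says when an increase cannot be accepted, and a committee that reviews prehospital times could still object. This stands, and it limits the point to what the condition could permit. The point survives because no other condition is given.

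**It may be a drafting slip.** The main term in the sentence is onset-to-needle time, and the problem arises only if the parenthesis overrides it. That is plausible, but the text does not settle it.

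**The article is condensed.** The full protocol or a committee charter may be clearer. That would excuse missing detail. It does not excuse a sentence that conflicts with the article's own outcome table.

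**The look has probably happened.** The section on preintervention training says the format changed between activation of clusters three and four, and the trial status section has recruitment ending on July 1, 2021. The trigger had therefore passed before publication. This stands and changes the remedy from prevention to disclosure and consistent reporting.

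**Stronger inferences that the article does not support.** A reader might conclude that every interim comparison is confounded with time. With five stations crossing over one at a time after an all-control period, the second and third periods have concurrent groups (1 against 4 stations, then 2 against 3), and the article does not state the interim model. A reader might also conclude that the look has too few patients to show a significant increase. Any such figure needs a standard deviation and a thrombolysis rate that the article does not give. It also depends on the timing: 3 intervention against 12 control station-periods at the moment of activation, or 6 against 14 one period later. How the interim difference is tested or adjusted can properly be left to a charter or analysis plan.

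**Conclusion.** The sentence is wrong as written. It presents two intervals as one, against Table 2 and the Background, and the two readings give opposite answers on the same data whenever door-to-needle time falls by no more than onset-to-hospital time rises. In the assumed case of +15 and -5 minutes, the condition can be met with total delay 10 minutes longer.

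The contradiction itself rests on no assumption. The size does: the minutes are illustrative, and the identity holds only within treated patients. The documents do not show that patients were treated later, or that the committee used the door-to-needle reading. The primary outcome, the sample size and the main analysis are untouched. The point matters because this is the only acceptance condition stated for the safety committee.

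**What to change.** Reconcile the committee section with Table 2 and the Background. The sponsor and the committee should:

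1. Name the single interval that governs the condition, noting that door-to-needle time does not contain the prehospital delay. Which interval it should be is for them to decide.
2. State the patients in whom each part of the condition is assessed.
3. State which interval was applied at the interim look, if it has taken place, and use the same definition in the final safety report.

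The cost is a sentence or two in the protocol and the committee's charter, and a line in the report. Onset-to-treatment and door-to-needle time are already planned outcomes, so the final report should need no new data items. The article does not show which needle times were available for control patients at the interim look: it describes registration on the dedicated iPad for intervention patients. The statement about that look should say what was used.

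### The interim rule weighs a prehospital delay against needle times that only thrombolysed patients have, so onset-to-needle time among the treated understates a real delay

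*Protocol article*

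**What the plan says.** The section on the data monitoring and safety committee fixes one interim look: "A data safety committee carries out an interim analysis after activation of cluster 3". On its content it says: "The committee reviews prehospital times and especially prehospital on-scene time". It then gives its only criterion: "A significant increase in onset-to-hospital time is acceptable only if onset-to-needle time (i.e. door-to-needle time) is reduced". The operative words are that a delay "is acceptable only if onset-to-needle time" falls. No treatment proportion is named.

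Table 2 lists onset-to-hospital time for both cohorts, that is, for all suspected strokes as well as final strokes. The needle-time entry is "Door-to-needle time in patients receiving IVT", so it is defined only in thrombolysed patients. The same table also collects "Number of patients receiving IVT" and the number receiving EVT, but the monitoring section does not use them.

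The Background reports that fewer than half of Norwegian stroke patients arrive within 4 hours, "which reduces the likelihood of successful acute treatment". The abstract puts the enrolment window at 24 hours from onset.

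**The concern.** The two halves of the criterion refer to different populations. The possible harm, a longer time to hospital, is measured in everyone. The condition set against it is measured only in patients who received IVT, and by the protocol's own account delay can decide who receives it. Because enrolment runs to 24 hours, a patient delayed past treatment stays in the trial but has no needle time. Such patients would have had the longest onset-to-needle times, so losing them pulls the summary down. This is selection on an event that occurs after the intervention.

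The trial's rationale is that more patients should receive acute treatment. A criterion that looks only at the treated cannot show a fall in their number.

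**Working it through.** The plan attaches no figure to this rule, so there is none to reproduce. What follows is an illustration. All its inputs are assumptions, and the cut-offs are modelling devices, not statements about eligibility.

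**Inputs.** Onset-to-hospital time T before any delay follows one of three patterns: uniform on 30 to 1440 min; lognormal with median 240 min and log-SD 0.8; or lognormal with median 240 min and log-SD 1.2 (both lognormals truncated at 1440 min). The 1440 min is the 24-hour enrolment window, and the 240 min echoes the 4-hour benchmark in the Background. Door-to-needle time is 40 min.

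**Formulas.** Let d be the added prehospital delay and s any in-hospital saving.
- Arrival cut-off c: treated if T ≤ c before the delay, and if T ≤ c − d after it.
- Onset-to-needle cut-off K: treated if T ≤ K − 40 before, and if T ≤ K − 40 − d + s after.
- With t0 and t1 the limits on T before and after, the relative loss of treated patients is 1 − F(t1)/F(t0).
- The observed change in mean onset-to-needle time is (d − s) − {E[T | T ≤ t0] − E[T | T ≤ t1]}. The true change for each patient is d − s.

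**Hand check (uniform, c = 240, d = 20, s = 0).** Before: treated share 210/1410 = 14.9%, mean T = (30 + 240)/2 = 135. After: T ≤ 220, so the share is 190/1410 = 13.5% and mean arrival is (30 + 220)/2 + 20 = 145. The observed rise is 10 min against a true 20. The relative loss is 1 − 190/210 = 9.5%.

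**A 20-min delay with no in-hospital saving (numerical integration).**

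| Pattern | Treated share, c = 240 | Relative loss | Observed rise | K = 240: loss, rise | K = 270: loss, rise |
|---|---|---|---|---|---|
| Uniform | 14.9% to 13.5% | 9.5% | 10.0 min | 11.8%, 10.0 min | 10.0%, 10.0 min |
| Lognormal 0.8 | 50.6% to 46.3% | 8.7% | 11.5 min | 12.3%, 10.6 min | 9.4%, 11.3 min |
| Lognormal 1.2 | 53.6% to 50.5% | 5.8% | 12.9 min | 7.8%, 12.3 min | 6.2%, 12.7 min |

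K = 280 gives the same results as c = 240 here, because 240 + 40 = 280. Across the table the observed rise is 10.0 to 12.9 min, so 1 − 12.9/20 = 35.5% to 1 − 10/20 = 50% of the delay is hidden. The relative loss is 5.8 to 12.3%.

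**Wider inputs.** With lognormal median 240 to 300 min, log-SD 0.8 to 1.2, door-to-needle mean 40 min (SD 12) and onset-to-needle cut-offs of 240 to 360 min, the observed rise is about 48 to 70% of the true delay. A 20-min delay then loses 3.5 to 14.5% of treated patients.

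**Can the mean fall despite a net delay?** Take d = 10 and s = 6, a true change of +4 min per patient.
- Arrival cut-off at 240: the mean changes by −1.0, −0.2 and +0.5 min in the three patterns; the median by −1.0, +0.3 and +1.2 min.
- Onset-to-needle cut-off at 240, 270 or 280: the mean rises by 2.0 to 2.6 min in all nine cases.

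The understatement appears under both kinds of cut-off. The reversal appears only under the arrival cut-off, where faster in-hospital work brings nobody back inside the limit.

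**The case against.** A reader might infer that the rule excuses a delay whenever needle time falls, so that the committee would pass a trial in which everyone is treated later and fewer are treated. The text does not support that. Its condition is necessary, not sufficient: it says what must hold before a delay is tolerated, not that the delay is then acceptable. The delay itself stays visible, because onset-to-hospital time is seen in all suspected strokes. With a 20-min delay and no in-hospital saving, the mean still rises and the condition correctly fails. The sign reversal depends on the model and, with medians, survives only in the uniform pattern.

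The trigger may also rarely fire. The three patterns have SDs of 243 to 407 min. Assuming 325 patients per arm at the interim (half of 1300, split evenly), the standard error of a mean difference is SD × √(2/325), or 19.1 to 31.9 min. By the normal approximation, power to flag a 20-min shift is then only about 10 to 18%.

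The inputs are open to challenge: the two lognormal patterns put slightly more than half of arrivals within 4 hours, whereas the Background says fewer than half. The wider set, with medians up to 300 min, gives the same direction. A fuller protocol or committee charter, not shown, may add items to the review.

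Finally, if the condition is reconciled to door-to-needle time, the loss of long onset times no longer biases it, because that interval starts at the door. The prehospital delay is then not counted at all, which is the separate wording problem in the same sentence.

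These points limit the concern to a minor one. They leave standing that the printed criterion depends on a group that the delay can shrink.

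**Conclusion.** The point holds in a limited form. Read as onset-to-needle time, the measure set against a prehospital delay understates that delay, because patients delayed out of treatment have no needle time. Under the assumed patterns a uniform 20-min delay shows as about 10 to 13 min, with about 6 to 12% fewer treated in relative terms. Direction and rough size are what this supports; the exact figures rest on assumed arrival times, door-to-needle time and cut-offs.

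An apparent reduction despite a net delay can occur but should not be presented as typical. Nor do the documents say that a shorter needle time alone makes a delay acceptable. This is a low-severity improvement to a monitoring criterion and does not touch the primary analysis.

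**What to change.** In the monitoring section, state that needle time among treated patients does not by itself establish that a delay is acceptable. Add that the committee also reviews, by study phase and with confidence intervals, the number and proportion receiving IVT and EVT.

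Use patients with a final stroke diagnosis as the main denominator and show all accepted patients alongside. The intended rise in positive predictive value (PPV) changes the mix of accepted patients. At a constant treatment rate r per stroke, moving PPV from 40% to 50% takes the treated proportion from 0.40r to 0.50r, a 25% rise. That could mask a loss per stroke of up to 1 − 0.40/0.50 = 20%.

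Set no automatic trigger for a lower proportion: without a margin, and with no true difference, it would be tripped about half the time. The sponsor and the committee should reconcile the Background, Table 2 and the monitoring section on what counts as acceptable delay.

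The cost is a sentence or two, since the treatment counts are already Table 2 outcomes. Final diagnoses, which are collected retrospectively, must be available at the interim. Treated counts will be small then, so the intervals will be wide and the proportions will inform judgement, not decide the matter.

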### Sample size calculation

Local registry data suggest that around 40% of patients admitted with stroke symptoms to the ED at OUH have a stroke diagnosis at discharge (700 stroke diagnoses out of 1800 admitted with suspected stroke during 2017 (unpublished data)). The prehospital pathway is not specified in the historical data. We aim for a 10% increase in the proportion of patients with a stroke diagnosis at discharge.

We used a two-sided test with alpha 5% and beta 80% and need a total of 808 patients to reach statistical significance. Due to the challenges of prehospital research in terms of large natural variation and loss to follow-up, we aim for a 50% patient surplus and intend to include 1300 patients. We estimate a 72-week study period to be sufficient to reach our goal. With all five stations including control patients before a stepwise cross-over to intervention, we end up with six 12-week periods. After the last cross-over, all paramedics have received training in the ParaNASPP model, and inclusion to the control group ends at this point. The study will be terminated after 72 weeks regardless of the number of patients included in the two groups.

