**Methods:**

A stepped wedge cluster randomised controlled intervention design will be used in this trial in Oslo, Norway. Paramedics at five ambulance stations will enrol adult patients with suspected stroke within 24 h of symptom onset. All paramedics will begin in a control phase with standard procedures. Through an e-learning program and practical training, a random and sequential switch to the intervention phase takes place. A mobile application for NIHSS scoring, including vital patient information for treatment decisions, transferring data from paramedics to the on-call stroke physician at the Stroke Unit at Oslo University Hospital, will be provided for the intervention.

The primary outcome measure is positive predictive value (PPV) for prehospital identification of patients with acute stroke defined as the proportion of patients accepted for stroke evaluation and discharged with a final stroke diagnosis. One thousand three hundred patients provide a 50% surplus to the 808 patients needed for 80% power to detect a 10% increase in PPV.

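### The 808-patient, 80% power figure is for individual randomisation; with period and station adjustment, 1300 patients give about 58–75% power for a 10-point gain over ICC 0–0.02

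*Protocol article*

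**What the plan says.** The sample size section takes as baseline that "around 40% of patients admitted with stroke symptoms to the ED at OUH have a stroke diagnosis at discharge", citing 700 of 1800 in 2017. It then says "We aim for a 10% increase in the proportion of patients with a stroke diagnosis at discharge" and "We used a two-sided test with alpha 5% and beta 80% and need a total of 808 patients to reach statistical significance". It adds "we aim for a 50% patient surplus and intend to include 1300 patients", giving natural variation and loss to follow-up as the reasons. The abstract puts it as "One thousand three hundred patients provide a 50% surplus to the 808 patients needed for 80% power to detect a 10% increase in PPV".

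The design described under Study design and Sample size calculation is a stepped wedge: five ambulance stations, six 12-week periods, one station crossing over at each step. The calculation mentions no intracluster correlation (ICC), design effect or period adjustment. The Statistics section makes the PPV comparison primarily on all included patients pooled, and leaves hierarchical models for the temporal design to be explored.

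**The concern.** In a stepped wedge the share of patients under intervention rises from none in the first period to all in the last. An estimate that does not adjust for period therefore mixes the intervention with whatever else changed over calendar time. An estimate that does adjust uses only the within-period contrasts between stations and, through the station effect, part of the within-station contrasts. That costs precision before any correlation is considered. A number computed for two independent groups carries no such cost.

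Two things are at stake. If the adjusted model is used, the advertised power is too high, and a non-significant result could be over-read as evidence of no effect from a trial with a comfortable surplus. If the pooled test is used, the power figure fits, but the test can be biased by time trends and its type I error exceeds 5% when stations differ. The sample size and the primary analysis therefore have to be settled together.

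**Working it through.** **Inputs.** From the article: control PPV 0.40, intervention PPV 0.50, two-sided 5%, 80% power (abstract), N = 808 and 1300, 5 stations, 6 periods. The 10% is read as absolute; a relative 10% (40% to 44%) would need about 4,780 patients. Assumed: equal cells of m = N/30 patients; s² = 0.45 × 0.55 = 0.2475; the ICC; the cluster autocorrelation (CAC).

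**1. Reproducing 808.** Unpooled two-proportion size per arm: n = (0.40×0.60 + 0.50×0.50)(1.960 + 0.842)²/0.10² = 384.6. With continuity correction: n/4 × [1 + √(1 + 4/(n × 0.10))]² = 404.35. Two arms give 808 by nearest rounding (810 rounded up). Other versions give 770 (unpooled, uncorrected), 776 (pooled, uncorrected) and 816 (pooled, corrected). This accounts for the whole figure, with nothing left over for the design.

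**2. Cost of period adjustment alone (ICC 0).** With k of 5 stations on intervention in a period, the information is m × k(5 − k)/(5s²). Summing over k = 0 to 5 gives m(4 + 6 + 6 + 4)/(5s²) = 4m/s². At N = 1300, m = 43.33, so the variance is 0.2475/173.33 = 0.001428 and SE = 0.0378. The pooled comparison has variance 4 × 0.2475/1300 = 0.000762. The ratio is 1.875; the planned inflation is 1300/808 = 1.61. Power = Φ(0.10/0.0378 − 1.96) = 75%.

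**3. Adding station correlation.** Hussey–Hughes generalised least squares variance: categorical periods, random station effect, CAC 1, normal reference, N = 1300.

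| Assumed ICC | SE | Power for 10 points | Difference detectable at 80% power | N for 80% power |
|---|---|---|---|---|
| 0 | 0.0378 | 75% | 10.6 points | about 1460 |
| 0.005 | 0.0431 | 64% | 12.1 points | about 2010 |
| 0.01 | 0.0450 | 60% | 12.6 points | about 2190 |
| 0.02 | 0.0464 | 58% | 13.0 points | about 2290 |

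At N = 808 the power is 55% (ICC 0), 44% (0.01) and 41% (0.02).

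**4. Relaxing the assumptions at N = 1300.**
- CAC 0.8: 58% at ICC 0.01 and about 53% at ICC 0.02.
- A t reference with 4 df: 52% at ICC 0 and 40% at ICC 0.01.
- Unequal stations, in the layouts and orders tried: at ICC 0, power runs from about 64% to 81%. At ICC 0.001 none exceeded 75.5%, and at ICC 0.01 and 0.05 power was lower still.

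**5. The pooled test at N = 1300.** SE = √0.000762 = 0.0276, so nominal power is Φ(0.10/0.0276 − 1.96) = 95%. With stations spending 5, 4, 3, 2 and 1 of 6 periods on intervention, the station effects enter the pooled difference with weights (4, 2, 0, −2, −4)/15, whose squares sum to 40/225 = 0.178. At ICC 0.01 the true variance is (0.01 × 0.178 + 0.99 × 4/1300)s² = 0.00482s², against a nominal 0.00308s²: a ratio of 1.57. The type I error is then 2[1 − Φ(1.96/√1.57)], about 12%. The same calculation gives 32% at ICC 0.05. Simulation gave 13% and 34%. None of this includes a time trend.

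**6. The two slips.** 808 × 1.5 = 1212, and 1300/808 = 1.609, a 61% surplus. Taken literally, a beta of 80% is 20% power.

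**The case against.** The strongest reply is that 808 suits the analysis the article declares. The Statistics section makes the pooled comparison primary, and that test has about 95% nominal power at 1300. A model with a random station effect but no period terms would also keep about 91–95% over ICC 0–0.02 with CAC 1. So a reader might infer that this stepped wedge cannot reach 80% power whatever the analysis; the article does not support that. The shortfall belongs to a period-adjusted analysis.

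This limits the point but does not remove it. The 95% holds only with no time trend and no station correlation. The Statistics section itself foresees temporal trends. The article also reports an inclusion pause of almost seven months for COVID-19 and a switch to digital training between the third and fourth clusters, so a calendar effect is plausible.

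Two further replies stand in part. The shortfall that needs no assumed ICC is modest: 75% against 80%, or 10.6 points against 10. With strongly unequal stations in a favourable order and ICC exactly 0, power can just pass 80%. The larger shortfalls rest on ICCs that the article does not supply.

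The slips should not be over-read either. The abstract's "808 patients needed for 80% power to detect a 10% increase in PPV" shows that 80% power was meant. The target of 1300 exceeds 1212, so the surplus error does not flatter the trial.

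**Conclusion.** The concern holds in conditional form. The 808 figure is an individual-randomisation size, and its 80% power is not a property of the five-station, six-period design once period is adjusted for. With equal cells, CAC 1 and a normal reference, 1300 patients give about 75% power at ICC 0 and 58–60% at ICC 0.01–0.02. Lower autocorrelation or a small-df reference reduces this further. Because period adjustment alone costs a factor of 1.875 against an inflation of 1.61, the equal-cell shortfall does not depend on a guessed ICC, although its size does. The mismatch with the pooled primary comparison is part of the same defect. Restating power alone would quote it for an analysis that the article only says will be explored. The surplus percentage and the beta are plain errors, but editorial.

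**What to change.** - Label 808 as the size for individual randomisation (40% v 50%, continuity-corrected).
- In the Statistics section, make the period- and station-adjusted model the primary PPV comparison and keep the pooled comparison as supportive. Record this as a protocol amendment.
- Restate power for that model at 1300 patients: about 58–75% for a 10-point increase over ICC 0–0.02, or a detectable difference of about 11–13 points at 80% power. List the assumptions (equal cells, CAC 1, normal reference, assumed ICCs) and the lower values when they are relaxed: about 53% with CAC 0.8 at ICC 0.02, and about 40% with 4 df at ICC 0.01.
- In the abstract and the sample size section, correct the surplus to 61% or the target to 1212. In the sample size section, replace beta 80% with power 80%.

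The cost is a few sentences, a less favourable stated power and a wider primary confidence interval. No extra enrolment is asked for.
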